### Outcome measures

The primary outcome of the study is the EMG activity of the upper trapezius muscle after a single session of acupuncture. The secondary outcomes for the study are the numerical rating scale score for pain, pain area and cervical range of motion.

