Changes in muscle activity are generally characterized by the variation and/or reduction in the firing rate of the motor units [20,21], reflecting changes in the myoelectrical pattern of the muscle that can be measured through sEMG [21,22]. Thus, sEMG has been used to determine whether the stimulus from acupuncture has an effect on the activity of skeletal striated muscle [19,23-26]. Some studies have demonstrated a remote effect from acupuncture in the upper trapezius muscle [19,26]. However, further investigations have not found any clinical benefits relating to this discovery. The description of the relationship between the upper trapezius muscle and the acupoints denominated triple energizer 5 (TE-5; ‘*Wai-guan*’) and large intestine 11 (LI-11; ‘*Qu-chi*’) [26] allow the use of sEMG to clarify whether acupuncture truly has a neurophysiological effect on this muscle, the motor control of which is affected in individuals with NS-NP [5].

In clinical practice, the confirmation that acupoints TE-5 and LI-11 act directly on the upper trapezius muscle in patients with NS-NP could contribute toward: i) the standardization of these acupoints as stimuli for the treatment of changes in the upper trapezius muscle stemming from mechanical injury, myofascial tension with and without the presence of trigger points and systemic diseases, such as fibromyalgia; ii) improving the estimation of the effects of treatment; iii) making the use of acupuncture less complex; iv) stimulating the use of acupuncture alone or in combination with other forms of treatment (physical therapy, exercise, massage or manual therapy) and v) allowing the testing of other noninvasive stimuli, such as low-level laser therapy.

The objectives of this study are:To determine whether stimulation with acupuncture at acupoints TE-5 and LI-11 affects sEMG activity of the upper trapezius muscle in healthy subjects and patients with NS-NP andTo determine whether stimulation with acupuncture at acupoints TE-5 and LI-11 contributes to improvements in pain and cervical range of motion in patients with NS-NP.

The first hypothesis is that stimulation with acupuncture at acupoints TE-5 and LI-11 acts directly on sEMG activity of the upper trapezius muscle in healthy subjects and individuals with NS-NP. The second hypothesis is that stimulation with acupuncture at acupoints TE-5 and LI-11 provides immediate improvements in pain and cervical range of motion in patients with NS-NP.

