**Figure 3 Fig3:**
[figure not shown]
**Details of experimental setup.** Two straps over the acromion -one attached directly to the chair and one attached to the support of a load cell **(A)**; Force and electromyography activity (**(B)** surface electrode) of the upper trapezius muscle will be measured simultaneously during shoulder elevation movements. Feedback will be provided from the projection of a 20-inch screen on a white wall in front of the subject.

The maximum value in Newtons (N) will be considered the MVC. After three minutes of rest following the last MVC, the first sEMG signal (EMG-1) will be collected. The volunteer will be instructed to perform a ‘step contraction’, consisting of five force levels (10, 15, 20, 25 and 30% MVC). To investigate possible myoelectric manifestations of fatigue, a repetition of the third step (20% MVC) will be added as the sixth step to determine differences in the sEMG variables between these two steps [22]. Contraction time will be 11 seconds for each force level. Feedback of the step contraction will be provided from the projection of a 20-inch screen on a white wall in front of the subject. All participants will receive training prior to the shoulder elevations, based on the previously determined force levels.

New evaluations of pain and cervical range of motion (EV2) will be performed after one minute of rest. Acupuncture will then be performed, with the needles remaining inserted for 30 minutes. After the removal of the needles, further evaluations of pain and cervical range of motion will be performed (EV3), followed by a second EMG reading (EMG-2) in the same manner as performed during EMG-1. A fourth evaluation of pain and cervical range of motion (EV4) will be performed after two minutes of rest.

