### Electromyography signal processing

For the analysis of the sEMG signal, the first second of each step (considered as a transition time between force levels) will be discarded and the subsequent 10 seconds will be divided into one-second windows. The root mean square (RMS) and median frequency (MDF) of the power spectrum will be calculated for each window. All EMG signals will be processed performing specific routines carried out in the Matlab program, version 7.1 (MathWorks Inc., Natick, Massachusetts, United States).

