### Data analysis

Linear regression analysis will be applied for each individual to investigate associations between the sEMG variables and force (excluding the sixth step). The slopes of the regression lines will be used to measure the sensitivity of the sEMG variables regarding changes in force. The Shapiro-Wilk test will be used to test the normality of the data distribution regarding RMS and MDF values in the third and sixth step of the step contraction. Paired samples (Student’s t-test or Wilcoxon test) will be used to test differences between third and sixth contraction step. A mixed linear model will be used to analyze and compare the slopes of the regression lines during sustained contraction (five steps) between pre-acupuncture (EMG-1) and post-acupuncture (EMG-2) evaluations. These comparisons will demonstrate whether acupoints TE-5 and LI-11 affect the activity of the upper trapezius muscle, as hypothesized. The pain (numerical rating scale and pain area) and cervical range of motion data collected during the four evaluations will also be compared using a mixed linear model. The Statistical Package for Social Sciences (**IBM SPSS Statistics**, version 20.0, IBM™, Armonk, New York, United States) for Windows) will be employed for the statistical analysis, with the level of significance set to 5% (*P* <0.05).

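### The primary outcome, EMG activity, is tested through at least two variables at an unadjusted 5%, and the plan does not say which one decides the claim

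*Protocol article*

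**What the plan says.** **Outcome measures** (Protocol article) gives a single primary outcome: "The primary outcome of the study is the EMG activity of the upper trapezius muscle after a single session of acupuncture". No variable, summary, contrast or group is attached to it.

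**Electromyography signal processing** derives two variables from the recording: "The root mean square (RMS) and median frequency (MDF) of the power spectrum will be calculated for each window".

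**Data analysis** regresses the EMG variables on force for each person and uses a mixed linear model to "compare the slopes of the regression lines during sustained contraction (five steps) between pre-acupuncture (EMG-1) and post-acupuncture (EMG-2) evaluations". The next sentence gives that analysis its role: "These comparisons will demonstrate whether acupoints TE-5 and LI-11 affect the activity of the upper trapezius muscle, as hypothesized". The same section states one threshold for everything ("with the level of significance set to 5" per cent) and gives no order of testing or adjustment.

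**Background** extends the EMG hypothesis to both groups: the stimulation "acts directly on sEMG activity of the upper trapezius muscle in healthy subjects and individuals with NS-NP".

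**Sample size calculation** uses EMG amplitude only, before needling and after three minutes of manipulation, and arrives at 12 per group.

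Data analysis also contains a separate EMG comparison: "Paired samples (Student’s t-test or Wilcoxon test) will be used to test differences between third and sixth contraction step". **Experimental procedures** explains its purpose: "To investigate possible myoelectric manifestations of fatigue, a repetition of the third step (20% MVC) will be added as the sixth step".

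**The concern.** A primary outcome should lead to one decision, or to several under a stated rule. Here the outcome is singular by name but plural in analysis. At least two slope comparisons (RMS and MDF) are presented as what will settle the hypothesis, each at 5%. Nothing says which one decides, or whether one or both must be significant. A result on either could be reported as showing that the acupoints act on the muscle, and the error rate of that claim would then exceed the stated 5%.

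The sections also point to different endpoints. The sample size rests on an amplitude level, while the hypothesis is tested on slopes of two variables. MDF and both slopes have no planning value.

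**Working it through.** **Inputs**

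| Input | Value | Source |
|---|---|---|
| EMG variables | 2 (RMS, MDF) | Electromyography signal processing |
| Contrast tied to the hypothesis | slope, EMG-1 versus EMG-2 | Data analysis |
| Groups in the hypothesis | 2 (patients, healthy) | Background |
| Significance level | 0.05, unadjusted | Data analysis |
| Amplitude before / after | 21.3 ± 9.5 / 9.5 ± 3.5 μV | Sample size calculation |
| Design power, n | 0.99, 12 per group | Sample size calculation |
| RMS–MDF correlation r | not given; assumed 0 to 1 | assumption |
| Groups tested separately or pooled | not stated; both shown | assumption |
| One significant result suffices | not stated | assumption |

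**Step 1: the plan's own figure.** The difference is 21.3 − 9.5 = 11.8. The pooled SD is √((9.5² + 3.5²)/2) = 7.159, so d = 11.8/7.159 = 1.648. The two-sample normal formula is n = 2(z_α + z_β)²/d².
- One-sided 5%, 99% power: n = 12.
- Two-sided: n = 14.

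The stated 12 is therefore reproduced, from amplitude alone and one contrast. (The article does not state sidedness.)

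**Step 2: how many tests bear on the primary claim.**
- Groups pooled in one model: RMS slope and MDF slope, 2 tests.
- Groups tested separately: 2 variables × 2 groups = 4 tests.

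**Step 3: chance of at least one false positive.** For k independent tests it is 1 − 0.95^k.
- k = 2: 1 − 0.95² = 9.75%.
- k = 4: 1 − 0.95⁴ = 18.55%.

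The two variables come from the same signal, so they may be correlated. Simulating two jointly normal two-sided tests per group, with the groups independent because they are different people, gives:

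| Assumed r | 2 tests (pooled) | 4 tests (separate groups) |
|---|---|---|
| 0 | 9.75% | 18.5% |
| 0.3 | 9.5% | 18.1% |
| 0.5 | 9.1% | 17.4% |
| 0.7 | 8.3% | 16.0% |
| 0.9 | 7.0% | 13.5% |
| 1 | 5% | 9.75% |

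Independence gives the largest value in each column. Correlation of either sign lowers it.

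**Step 4: effect of controlling the error.** One named test at 0.05 has a 5% error. With four confirmatory tests, Bonferroni uses 0.05/4 = 0.0125 each. The familywise error is 1 − 0.9875⁴ = 4.9% under independence and at most 5% under any correlation.

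Power for a paired two-sided t-test with n = 12 on the plan's amplitude figures uses SD_diff = √(9.5² + 3.5² − 2·ρ·9.5·3.5), where ρ is the before/after correlation (assumed). The non-centrality is (11.8/SD_diff)·√12, with 11 degrees of freedom.
- ρ = 0: SD_diff = 10.12; power 96% at 0.05, 83% at 0.0125.
- ρ = 0.5: SD_diff = 8.32; power 99% at 0.05, 95% at 0.0125.

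These figures apply to the before/after amplitude level. They do not apply to a slope or to a difference from sham, for which the article gives no planning values.

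**The case against.** **Multiplicity rules usually sit in a full protocol or SAP, and this is a condensed article.** That is fair. The absence of an adjustment rule would not be a point by itself. But the article does define the primary outcome, does name the tests that decide it and does fix their level. As stated, these do not identify one primary endpoint, and choosing the variable belongs to the outcome definition.

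**One significant result may not be enough.** The hypothesis names healthy subjects and patients together, so it can be read as requiring an effect in both. On that reading the second group adds no inflation. Nor does the article say that the groups are tested separately; it specifies a mixed linear model. Both objections stand, which is why the size is given conditionally. Neither settles the choice between RMS and MDF.

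**Larger figures are tempting but unsupported.**
- A reader might take 18.5% as a minimum. It is the independence value for four tests, and correlation lowers it.
- A reader might add the third-versus-sixth-step comparisons. Counted as 2 variables × 2 groups × 2 treatments × 2 recordings, they give 1 − 0.95¹⁶ = 56%. The article presents them as a fatigue check, says nothing of that 16-way split, and attaches the statement about demonstrating the hypothesis to the slope model. A difference between two steps within one recording is not a test of acupuncture.
- A reader might add the pain score, pain area and six neck movements: 1 − 0.95⁸ = 34%. These are labelled secondary and cannot produce a false primary claim.

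**Conclusion.** The point holds, at a moderate size. The primary outcome is not reduced to one test, at least two slope comparisons bear on it at an unadjusted 5%, and only amplitude has a sample-size basis.

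If either variable is enough for the claim, the familywise error is about 5% to 10% in one pooled model. It is about 10% to 18.5% if the groups are tested separately and any one of four results suffices. Within each range the position depends on the RMS–MDF correlation, which the article does not give. Only perfect correlation in a pooled model, or a rule requiring every result to be significant, brings the error to 5% or below.

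The plan is usable, but its primary claim should be tied to one test before the data are analysed.

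**What to change.** In Outcome measures and Data analysis, name one primary EMG test at 5% by stating:
- **Variable:** RMS, the amplitude measure, which matches the variable behind the sample size.
- **Summary:** the slope on force or the level. The sample size used a level and the analysis uses a slope, so the choice must be explicit.
- **Group:** one, named.
- **Contrast:** preferably the tACP versus sACP difference in the change from EMG-1 to EMG-2, so that the randomised sham comparison is used.

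Make MDF, the other group and the third-versus-sixth-step comparison secondary or supportive. If several EMG tests are to stay confirmatory, state a fixed order or use Holm.

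**Cost.** MDF and the other group lose confirmatory status. This goes beyond wording if the contrast or summary changes. The sample-size statement rests on a before/after amplitude difference with no sham comparator, so it must be aligned with the chosen contrast and may need planning values that the article does not contain. If four tests are kept, the power on the amplitude figures in the working (83% to 95% at 0.0125) suggests that control is affordable at n = 12 for that contrast only.

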### Measures

#### Numerical rating scale for pain

A numerical rating scale for pain will be used to assess pain intensity in the NPG. This is an 11-point scale ranging from 0 (absence of pain) to 10 (worst possible pain) [28]. The numerical rating scale has been translated and cross-culturally adapted for the Brazilian population [29].

#### Pain area

The individuals in the NPG will be asked to draw the distribution of their overall pain symptoms on an anatomical body map. The drawings will be subsequently digitized using the ACECAD D9000 (ACE CAD Enterprice Co Ltd, Taipei Hsien, Taiwan) and pain areas will be measured.

#### Cervical range of motion

A range of motion instrument will be used to determine cervical spine movements (Model: CROM Basic, Performance Attainment Associates, Roseville, Minnesota, United States). This instrument is composed of two gravity goniometers and a compass goniometer, and has been demonstrated to be a reliable tool, with adequate validity [30]. The device will be placed on the top of the head and the patient will be instructed to move the head as far as possible, without experiencing pain, in a standard fashion: right rotation, left rotation, flexion, extension, right lateral flexion and left lateral flexion. Three trials will be conducted in randomized order for each direction of movement and mean values will be recorded for analysis.

#### Electromyography

The sEMG signal will be recorded in the dominant upper trapezius muscle in the CG and on the side with the greatest self-reported pain in the NPG. EMG signals will be obtained using an eight-channel module (Model: EMG830C, EMG System do Brazil Ltda™, São José dos Campos, São Paulo, Brasil ), with a band pass filter with cut-off frequencies of 20 to 500 Hz, an amplifier gain of 1,000 and a common rejection mode ratio of less than 120 dB. All data will be acquired and processed using a 16-bit analog-to-digital converter, with a sampling frequency of 2 kHz.

Bipolar surface circular electrodes (Ag/AgCl, Medi-Trace™, Minneapolis, Minessota, United States) with a 10 mm diameter, will be used for the surface recording of EMG, with a center-to-center distance of 20 mm. Before electrode placement, the skin will be cleaned using abrasive paste (EASYCAP™, Woerthsee-Etterschlag, Germany). The electrode will be positioned 2 cm lateral to the midpoint of the line between the C7 spinous process and the acromion [31].

### Acupuncture

In the NPG, the upper trapezius muscle with the greatest area of pain will be chosen for acupuncture. Sterile acupuncture needles measuring 0.25 × 13 mm (Suzhou Huanqiu Acupuncture Medical Appliance Co. Ltd.™, Suzhou, Jiangsy, China) will be inserted in TE-5 (located on the dorsal face of the forearm between the radius and ulna, 3 cm above the joint line of the wrist) and LI-11 (located at the outermost point of the skinfold of elbow flexion, in the direction of the lateral epicondyle of the elbow) [26]. In the CG, the needles will be inserted 1 cm to the side of TE-5 and 1 cm to the side of LI-11 (in the direction of the styloid process of the radius).

Needle insertion will be performed by a physiotherapist with 10 years of experience who is certified in the use of acupuncture. The following insertion procedures will be carried out: i) participant seated comfortably with the upper limb unclothed; ii) cleaning of the skin with alcohol at the points to receive the needles; iii) needle depth in the NPG will be until the participant feels a sensation of mild shock (denominated *de-qi*) and needle depth in the CG will be superficial (just enough to maintain the needles fixed during the experiments and not enough to produce *de-qi*) and iv) in both groups, the needles will be rotated in both the clockwise and counter-clockwise directions for 10 seconds, every three minutes, at an approximate frequency of 60 times a minute. After the experiment, all participants in the NPG will be sent for physical therapy at the rehabilitation clinic of the University Nove de Julho.

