**Methods/Design:**

A total of 12 patients with nonspecific neck pain and 12 healthy subjects will be enrolled in a randomized, single-blind crossover study. Each subject will receive two forms of treatment in random order: a single session of traditional acupuncture (acupoints: triple energizer 5, ‘*Wai-guan*’ and large intestine 11, ‘*Qu-chi*’) and sham acupuncture. To eliminate carry-over treatment effects, a one-week wash-out period will be respected between sessions. Surface electromyography will be used to determine motor control in the upper trapezius muscle before and after treatment. The outcome measures in the group with neck pain will be a numerical pain rating scale (range: 0 (no pain) to 10 (maximum pain)), documentation of the pain area on a body chart and cervical range of motion. Comparisons before and after acupuncture treatment will demonstrate whether acupoints affect the activity of the upper trapezius muscle, pain and cervical range of motion.

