## Methods/Design

### Overview of research design

A randomized, single-blind, sham-controlled, crossover clinical trial will be carried out. The crossover design will be used to exclude the potential interference of individual differences. Figure 1 displays the flow of the study.

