**Flowchart of the study.**

### Study setting

Potential participants will be recruited from patients sent for the treatment of neck pain at the rehabilitation department of the University Nove de Julho. Undergraduate students from the same university will also be asked to participate in the study as the control group (CG).

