### Randomization and blinding

Each patient will receive two forms of acupuncture in random order: a single session of traditional acupuncture (tACP) and sham acupuncture (sACP). To eliminate carry-over treatment effects, a one-week wash-out period between the treatments will be respected. Randomization in each group will be performed by lots using opaque envelopes containing either the letter A, corresponding to tACP, or B, corresponding to sACP. The participants in each group will be distributed in two subgroups of six individuals based on the initial treatment (tACP and sACP), as shown in Figure 1. When one of the subgroups has completed the treatment course, the order of consecutive arrival of the volunteers will be used until all individuals have been allocated.

Measurements will be performed by five independent researchers. Researcher one will be in charge of the screening process, administration of the questionnaire and randomization of the treatments. Researcher two will be in charge of collecting the EMG data. Researcher three will administer the acupuncture treatment. Researcher four will be in charge of the analysis and processing of the EMG data. Researcher five will be in charge of the statistical analysis of the EMG, pain and cervical range of motion data. The participants will be blinded to the type of treatment and will not be informed that one of the two treatments is a sham procedure. Researchers four and five will also be blinded to both the group allocation and type of treatment.

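### The Acupuncture section assigns needle site and depth by disease group, contradicting the crossover in which every participant receives both real and sham needling

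*Protocol article*

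**What the plan says.** **The crossover.** Overview of research design: "A randomized, single-blind, sham-controlled, crossover clinical trial will be carried out". The abstract, having enrolled 12 patients and 12 healthy subjects, continues: "Each subject will receive two forms of treatment in random order". Randomization and blinding repeats this ("Each patient will receive two forms of acupuncture in random order") and adds: "The participants in each group will be distributed in two subgroups of six individuals based on the initial treatment (tACP and sACP"). Envelopes carry A for tACP or B for sACP. Treatment is therefore a condition that every person passes through, with six people per starting treatment in each group.

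**Who the CG is.** Study setting: "Undergraduate students from the same university will also be asked to participate in the study as the control group (CG"). Inclusion criteria gives the CG its own entry rule, an absence of neck pain history. CG and NPG (neck pain group) are thus labels for disease status.

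**How needles are placed.** The Acupuncture section opens with the NPG, for whom needles "will be inserted in TE-5 (located on the dorsal face of the forearm between the radius and ulna"), and also in LI-11. It then says "In the CG, the needles will be inserted 1 cm to the side of TE-5 and 1 cm to the side of LI-11". On depth, NPG needles go in until de-qi is felt, while "needle depth in the CG will be superficial" and is not meant to produce de-qi. Neither tACP nor sACP is mentioned in that section.

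**The concern.** The Acupuncture section is the only place that gives needle depth or an off-point site, so it is what a practitioner or a later reader would turn to for the two techniques. As worded, it describes real needling for patients and sham needling for healthy students. That is a two-group comparison of patients with students, not a crossover.

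What is at stake is the sham control. In a crossover, each person's real session is set against the same person's sham session, and order is randomised. If technique follows disease group, that comparison disappears, and any difference between real and sham is also a difference between people with and without neck pain. Objective 1 in the Background also calls for stimulation at TE-5 and LI-11 in healthy subjects, which the Acupuncture section as written would not deliver.

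**Working it through.** **Step 1: could CG be shorthand for the sham condition?** Study setting, Inclusion criteria and the abbreviation list all use CG and NPG as groups of people. The Electromyography section does the same: dominant side in the CG, most painful side in the NPG. The Acupuncture section itself begins with the NPG's painful muscle and ends by referring NPG participants for physical therapy. A sham reading would need NPG to change meaning partway through the section. The group-based wording occurs twice, once for site and once for depth, so it is not a single slip.

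**Step 2: what is specified for each combination?**

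| | Site | Depth |
|---|---|---|
| Patients, real | TE-5, LI-11 (abstract; Acupuncture) | until de-qi (Acupuncture) |
| Patients, sham | not given | not given |
| Healthy, real | TE-5, LI-11 (abstract) | not given |
| Healthy, sham | 1 cm off each point (Acupuncture) | superficial (Acupuncture) |

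**Step 3: sessions by group and condition.** Inputs: 12 people per group, two sessions each, so 24 sessions per group and 48 in all.

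| | NPG real | NPG sham | CG real | CG sham |
|---|---|---|---|---|
| Crossover as randomised | 12 | 12 | 12 | 12 |
| Acupuncture section taken literally | 24 | 0 | 0 | 24 |

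The correlation between disease group and treatment in a 2 × 2 table is (ad − bc) / √(product of the four margins).

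- Crossover: (12×12 − 12×12) / √(24×24×24×24) = 0.
- Literal reading: (24×24 − 0×0) / √(24×24×24×24) = 576/576 = 1.

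**Step 4: what can be estimated?** Take a fixed-effects model with intercept, disease (g), treatment (t), period and g×t over the 48 sessions.

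- Crossover, six per sequence in each group: the design matrix has rank 5 of 5, so every term is estimable.
- Literal reading: t = g in every row, and so g×t = g. Three columns coincide, leaving intercept, g and period: rank 3 of 5 (3 of 4 with main effects only). The NPG-minus-CG difference estimates the sum of the disease, treatment and interaction effects, and nothing in the data separates them.

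People with one real and one sham session: 24 of 24 under the crossover, 0 of 24 under the literal reading.

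**Step 5: which hypotheses survive the literal reading?** Data analysis compares EMG-1 with EMG-2, and pain and range of motion across four evaluations.

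- Hypothesis 1, healthy subjects: not testable, since they would receive no needling at TE-5 or LI-11.
- Hypothesis 1, patients, and hypothesis 2: testable by pre/post change, without sham control.

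**Sample size.** The stated 12 per group does not bear on this point. It can be reproduced: difference 21.3 − 9.5 = 11.8; pooled SD √((9.5² + 3.5²)/2) = 7.16; the normal formula for two means at α = 0.05 and power 0.99 gives 12 one-sided and 14 two-sided. It is built from pre- and post-needling values, and reconciling the needling text leaves it unchanged.

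**The case against.** The best defence is that this is a labelling error with an obvious intended meaning. The abstract, the Overview and the Randomization section agree on a crossover, the envelope letter decides the treatment, and Objective 1 needs real stimulation in healthy subjects. One section departs from all of these, which fits NPG and CG having been written where tACP and sACP were meant. The article is also a condensed account: Figure 1, cited for the allocation, is not shown, and the full protocol or the practitioner's instructions may describe the techniques by condition.

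Most of this stands as an account of how the text probably arose, and it limits what may be inferred. It does not remove the contradiction. The article does not leave the sham procedure out; it states one and attaches it to the wrong variable for a crossover.

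Three stronger readings are tempting and go too far:

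- A reader might infer that neither hypothesis could be tested. Both are worded about stimulation at TE-5 and LI-11 without mention of sham, and the stated pre/post analysis would still address hypothesis 2 and the patient half of hypothesis 1, though uncontrolled.
- A reader might infer that real acupuncture for healthy subjects is wholly undefined. The abstract names the two active points for every subject; only the depth is missing.
- A reader might infer that a confounded design was chosen, or that randomisation was in fact void. The documents contain no evidence about how sessions were performed, and the design sections point the other way.

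Renaming the CG to keep it distinct from the sham condition would be a preference only, since the label is clearly defined.

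**Conclusion.** The contradiction is real and must be fixed. The Acupuncture section assigns site and depth by disease status, while the design sections assign treatment within person. Three items are missing as a result: sham site for patients, sham depth for patients, and active depth for healthy subjects.

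The size of the consequence is conditional. Only if the section were followed literally would the disease-treatment correlation go from 0 to 1 and the sham-controlled contrast be lost entirely. That rests on CG meaning the healthy students, as the article defines it, and on the same technique being used at both of a person's sessions, which is what the section's wording implies. This is an inconsistency in describing the intervention, not a finding about conduct.

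**What to change.** Reconcile the Acupuncture section with the abstract, the Overview of research design, and Randomization and blinding. If the crossover stands, key the text on needle site and depth to the treatment condition (tACP or sACP), stated as applying to both groups, in place of NPG and CG. Which technique belongs to which condition is for the investigators to state; the requirement here is that the sections agree.

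The cost is re-labelling in one section and, if they carry the same wording, in the practitioner's instructions. Sample size, randomisation and measurements do not change. Because Trial status says recruitment is under way, the technique used at each session already delivered should also be checked against that participant's allocated sequence and reported. Any session performed by group instead of by condition would not supply the intended contrast and would need to be identified before analysis.
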